### Treatment methods

2.3

This study includes personalized neoantigen peptide vaccine treatment and precision radiotherapy. The treatment sequence is radiotherapy first and then vaccine (**Figure 2**). The interval between precision radiotherapy treatment and peptide vaccine is 1 week.

**Figure 2 f2:**

Clinical study treatment regimen.

#### Precision radiotherapy

2.3.1

The course of treatment is 1 week, 3 times in total.

1. Critical lesion eliminating radiation therapy CLERT, in accordance with isotoxicity planning, radiation dose limits are based on standard NCCN (National Comprehensive Cancer Network) guidelines recommended for organs at risk (Organs at risk, OAR) limit dosage to 80% formulation.2. Critical lesions (Critical lesions) are defined as tumors in critical locations. If the tumor progresses in this location, it will lead to the patient’s death or severe symptoms, affecting the patient’s QOL (the quality of life). Life-threatening tumors such as: central lung cancer; tumors adjacent to large blood vessels, large tracheas, heart, esophagus and other mediastinal tumor lesions; metastatic tumors located in or adjacent to the brainstem. Situations that seriously endanger QOL include, but are not limited to, the following situations: tumors are in the spinal cord, esophagus, portal area, and load-bearing bones, or are close to the rectum, bladder, etc. The final decision was made by a panel of on-study radiation therapy experts.3. Radiotherapy, SBRT (stereotactic body radiation therapy), the protocol is 8–10 Gy × 3 versus 2 Gy × 3. The radiation dose limit is based on 80% of the OAR limit dose recommended by the standard NCCN guidelines. If the metastases are close to important structures such as the brainstem or esophagus, or have been previously treated with radiotherapy, the radiation dose limit allows the SBRT radiation dose to be adjusted to the OAR guideline limit dose.4. The key tumor is the treatment target area, which refers to the tumor tissue that mainly affects or threatens the patient’s life or QOL, regardless of the primary site or metastasis, as mentioned above. EDIC (The effective dose to the circulating lymphocyte EDIC, the equivalent dose of circulating lymphocytes) is an important reference indicator for formulating radiotherapy plans. The EDIC is limited to an effective dose that produces grade 2 or higher lymphocyte deficiency in less than 5% of patients. (Patented, part of the research data was disclosed by [name]/[name], et al. in ASTRO2017).

#### Polypeptide vaccine treatment

2.3.2

Five-month is a treatment course, and radiotherapy should be started within 1 week after the end of radiotherapy.

1. Receive neoantigen peptide vaccine “ prime phase” treatment on days 1, 4, 8, 15, and 22 of each treatment cycle;2. “Booster phase” treatment of neoantigen peptide vaccine at weeks 12 and 20;3. Each vaccination must be carried out after the side effects caused by the previous vaccination have subsided;4. Dosage and usage: The number of groups of polypeptide vaccine is determined according to the number of neoantigens identified in the patient, and is divided into 2–4 injection pools (1mL per injection). Each pool contains up to 5 peptides, with each peptide dosed at 0.3 mg. Peptides are dissolved in 500 μL of sterile solution and mixed with 500 μL of Poly I:C adjuvant at a concentration of 2 mg/mL prior to subcutaneous injection.5. Observation: Stay in the hospital for observation until side effects subside.6. Visit: At the end of each course of treatment, patients must return to the hospital for a visit and start the trial procedure for the next course of treatment.

#### Neoantigen polypeptide vaccine injection

2.3.3

The preparation, formulation and injection procedures of the neoantigen peptide vaccine are as follows (**Figure 3**):

**Figure 3 f3:**
[figure not shown]
Flow chart of neoantigen peptide vaccine injection.

##### Preparation of neoantigen peptide vaccine (step 01)

2.3.3.1

1. The drug transporter takes out the whole box of vaccine injection solution for this injection from the transport box, and the nurse confirms that the number on the sealing label of the packaging box is consistent with the injection order.2. The nurse opens the box and takes out the neoantigen peptide injection (each containing a neoantigen peptide library) and adjuvant poly IC injection (ampoule) in the vial. Poly I:C was used as an immunological adjuvant due to its ability to mimic viral double-stranded RNA, activate dendritic cells via TLR3 and MDA-5 (49), and promote antigen-specific T cell responses.3. The nurse checks the appearance of each vial:a. No leaks and cracksb. The injection solution in the bottle is colorless and has no visible particles.c. The bottle stopper is not damaged or loosed. The label number on the bottle is consistent with the bottle number indicated on the injection sheet

##### Mixture of neoantigen peptide vaccine and adjuvant (step 02)

2.3.3.2

1. The new antigen polypeptide vaccine injection solution can be placed on the table and thawed at room temperature. No special thawing treatment is required and do not shake it violently.2. Mixing of the new antigen peptide vaccine injection and the adjuvant. The specific operation is as follows:a. Take a bottle of neoantigen peptide injection (500 uL injection in a vial) and disinfect the bottle stopper with alcohol cotton;b. Take a bottle of poly I:C injection solution (ampoule), disinfect it with an alcohol cotton pad, break open the bottle cap, and use a 1mL disposable syringe to draw 500uL of poly I:C injection solution.c. Insert the syringe into the vial of research drug, and inject the poly I:C injection solution in the syringe into the first vial of polypeptide vaccine. After mixing, the mixed solution in the vial is 1 mL.d. Gently shake the tube upside down to mix the study drug injection and poly I:C injection adjuvant.

##### Injection of neoantigen peptide vaccine (step 03)

2.3.3.3

1. The injection sites were selected according to the numbering on the injection slip. The four vials of polypeptide vaccine were administered at the left axilla, left groin, right groin, and right axilla, which are lymph node-rich regions commonly used to enhance antigen presentation and immune activation.2. The requirements for subcutaneous injection are consistent with the conventional vaccination technique, that is, hold the skin taut with the left hand, hold the syringe with the right hand, fix the needle plug with the index finger, and the needle bevel should be upward at an angle of 30 to 40 degrees to the skin. Those who are too thin can pinch the injection site, quickly insert two-thirds of the needle, release the left hand to fix the needle plug, aspirate without blood return, and then inject the liquid medicine.3. Follow steps 1–2 to complete the injection of the other bottles of new antigen peptide vaccine at the corresponding sites.

### Eligibility criteria

2.4

#### Inclusion criteria

2.4.1

1. Voluntarily join this study;2. Age: 18–80 years old, male or female;3. Subjects with advanced tumors who have been diagnosed with advanced or recurrent malignant tumors by pathology and imaging, who have received systemic standard treatments that have failed or progressed before enrollment, and who currently have no effective first-line treatments (for effective treatments, please refer to my country’s “Clinical Oncology in China” Recommended by the latest version of the diagnosis and treatment guidelines issued by the “Academic Society”);4. There is at least one radiologically measurable lesion;5. Patients with expected survival time ≥ 3 months;6. Patients with ECOG (Eastern Cooperative Oncology Group) score of 0–2 points;7. Have had genetic testing, have genome/exome/transcription raw data that meets the basic requirements for neoantigen analysis and prediction, and predict more than one high-quality tumor neoantigen; or have prepared GMP-level neoantigen peptides and *in vitro* immunogenicity evaluation passed;8. Pregnant women, lactating women, and women of childbearing age who have had a negative pregnancy test within 7 days before enrollment, have no short-term birth plans, and are willing to take protective measures (contraception or other birth control methods) before and during the clinical trial;9. Good compliance, able to follow the research protocol and follow-up procedures.

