#### Exclusion criteria

2.4.2

1. No neoantigens were found in the sequencing data;2. Those with a history of bone marrow or stem cell transplantation;3. Currently participating in other therapeutic clinical trials; clinical trials of traditional Chinese medicine4. Active bacterial or fungal infection found clinically >= NCI-CTC (Common drug toxicity standards developed by the National Cancer Institute) CTCAE 5.0;5. Infection with HIV (human immunodeficiency virus), HCV (hepatitis C virus), HBV (hepatitis B virus), severe asthma, autoimmune disease, immune deficiency or patients treated with immunosuppressive drugs;6. People infected with herpes virus (except for scabs that last for more than 4 weeks);7. People with respiratory virus infection (except those who have been cured for more than 4 weeks);8. Severe coronary artery or cerebrovascular disease, or other diseases that the researcher believes should be excluded;9. Clinical, psychological or social factors affect informed consent or research conduct;10. Those with a history of drug or peptide allergy, or allergies to other potential immunotherapies;11. Patients without capacity for civil conduct.

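### Inclusion criterion 8 names pregnant and lactating women among those to be included; as printed, a lactating woman using contraception is eligible

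*Protocol article*

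**What the plan says.** Section 2.4.1 lists nine inclusion criteria. Item 8 begins "Pregnant women, lactating women, and women of childbearing age who have had a negative pregnancy test within 7 days before enrollment" and continues that such women "have no short-term birth plans, and are willing to take protective measures (contraception or other birth control methods) before and during the clinical trial". The item therefore names three groups and attaches three conditions: the test, the absence of birth plans, and contraception. It says nothing about stopping breastfeeding.

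Section 2.4.2 lists 11 exclusion criteria. None mentions pregnancy, lactation or breastfeeding. Two leave room for judgement: item 8, "Severe coronary artery or cerebrovascular disease, or other diseases that the researcher believes should be excluded", and item 9, "Clinical, psychological or social factors affect informed consent or research conduct".

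The crossover conditions in section 2.2 concern performance status, severe adverse events and organ function. The visit table in section 2.6 shows a pregnancy test at the end of treatment. Section 2.4.3 lets the researcher stop a patient's study treatment for other confirmed reasons.

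**The concern.** In an oncology trial of an investigational vaccine with radiotherapy, one expects pregnant and breastfeeding women in the exclusion list, and a negative test with contraception as an inclusion condition for women who could become pregnant. Item 8 merges the two, so groups that belong among the exclusions stand among those to be included.

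The fault lies in what item 8 states. The exclusion list's silence on lactation is not a separate fault, since a condensed article may leave detail to the full protocol. It matters only because nothing else printed corrects item 8.

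What is at stake is participant safety. A site that applied the criterion literally could enrol a breastfeeding woman, give her radiotherapy and, in the vaccine arm or after crossover, the peptide vaccine with its adjuvant. Contraception, the only protective measure the item specifies, does nothing for a nursing infant. The protocol recognises risk to offspring elsewhere: section 2.7.2 counts congenital anomalies in subjects' children as serious adverse events.

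**Working it through.** The article gives no figure to reproduce on this point. The check is a reading of item 8 in both possible senses, then of every other stated rule that might correct it.

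**Step 1: scope of the conditions in item 8.**

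| Reading | Pregnant woman | Lactating woman |
|---|---|---|
| A. The conditions govern all three groups | Fails the negative test, so the item contradicts itself | Eligible with a negative test, no birth plans and contraception |
| B. The conditions govern only women of childbearing age | Named for inclusion without condition | Named for inclusion without condition |

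Reading A is the natural one and the milder one. The item is wrong under both, and under both a lactating woman satisfies it.

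**Step 2: does another stated rule remove a lactating woman?**

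- Exclusion 8 (section 2.4.2) extends to "Severe coronary artery or cerebrovascular disease, or other diseases that the researcher believes should be excluded". Lactation is not a disease.
- Exclusion 9 is "Clinical, psychological or social factors affect informed consent or research conduct". An investigator might stretch this to cover breastfeeding, but it is not a rule about it.
- The remaining nine exclusions concern the absence of neoantigens, transplantation, other trials, infections and immune conditions, allergy and legal capacity. None reaches lactation.
- The crossover conditions (section 2.2) do not mention it, so a control patient admitted under item 8 could move on to the vaccine.
- The discretionary stopping reason (section 2.4.3) operates after enrolment and depends on the researcher.
- The pregnancy test in the visit table (section 2.6) falls at the end of treatment and would not detect lactation.

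No stated rule removes her.

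**Step 3: what a woman admitted this way would receive.** Inputs are from sections 2.3.1 and 2.3.2.

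- Radiotherapy: three fractions, of either 2 Gy or 8–10 Gy. The total to the target lesion is 3 × 2 = 6 Gy, or 3 × 8 = 24 to 3 × 10 = 30 Gy.
- Vaccinations per course: five in the prime phase (days 1, 4, 8, 15 and 22) and two boosters (weeks 12 and 20), so 5 + 2 = 7.
- Poly I:C per injection pool: 0.5 mL × 2 mg/mL = 1 mg. With 2–4 pools this is 2–4 mg per vaccination.
- Poly I:C per course: 7 × 2 = 14 mg to 7 × 4 = 28 mg.

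The radiotherapy applies in both arms. The vaccine and adjuvant figures apply in the vaccine arm or after crossover, and section 2.6 allows further courses. All of these are the mother's own exposure. The article gives no basis for estimating what, if anything, reaches an infant.

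**The case against.** The best counter-argument is that this is an evident wording slip and not a decision to enrol these women. The same sentence asks for a negative test and contraception, which shows the intent. There is other translation damage nearby: section 2.3.2, for example, has radiotherapy starting after radiotherapy ends. A pregnant woman cannot pass the item on its natural reading, so the practical defect concerns lactating women only. Those eligible have advanced or recurrent cancer after failed systemic treatment and stay on standard treatment during the 8-week vaccine preparation, so very few will be breastfeeding. The dose figures describe the mother and do not measure harm to an infant. Finally, a complaint that no rule protects the infant comes close to faulting a condensed article for an omission.

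Much of this stands. The slip is probable, the number affected is small, and the exposure figures do not size any infant risk. The point about omission also limits the criticism to the printed text of item 8.

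None of this repairs the item. An eligibility criterion is meant to be applied as written, and this one is an intact, grammatical sentence that admits the wrong patient. Allowance for what an article leaves out does not extend to what it states wrongly. Relying on an investigator to override the criterion defeats its purpose.

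**Conclusion.** Item 8 is wrong as printed. On the natural reading it contradicts itself for pregnant women and admits lactating women who meet its three conditions; on the alternative reading it admits both groups without condition. No other rule stated in the article corrects this.

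The reach is small: few patients, with no count available from the article. The consequence is confined to eligibility and safety. It does not touch randomisation, the PFS endpoint, the sample size or the analysis. It should be corrected because it is a misprinted safety rule in a trial reported as recruiting since January 2024 and planned to enrol over 2–3 years.

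The conclusion assumes that sites apply the criterion as the article prints it. If the full protocol, which is not shown, words item 8 correctly, the error is confined to the article and the correction is to the publication alone.

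**What to change.** Reword item 8 so that it covers only women of childbearing age: a negative pregnancy test in the 7 days before enrolment, no near-term plan to have a child, and contraception before and throughout the trial. Add pregnant or lactating women to the exclusion criteria in section 2.4.2. The working protocol should be checked for the same wording, and sites told if it carries it.

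The cost is one reworded inclusion item and one added exclusion line. Very few otherwise eligible patients would be lost, so the effect on recruitment is negligible, and no statistical element of the design needs to change.

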##### Neoantigen prediction

2.4.1.1

1. Sequencing Data Analysis: raw date of the WES and RNA sequencing need to be provided. Prioritize WES data that includes paired tumor tissue and negative control samples sequenced simultaneously.2. Neoantigen Prediction: neoantigen screening was conducted through three independent predictive analytics platforms, including TruNeo (46), ImmuneMirror (47), and Bayesian (48), and the resulting predictions were collected along with their corresponding neoantigen score rankings. By integrating the results from these three platforms, the top 20 overlapping mutant peptides were selected as targets for the neoantigen vaccine.

#### Exclusion criteria

2.4.2

1. No neoantigens were found in the sequencing data;2. Those with a history of bone marrow or stem cell transplantation;3. Currently participating in other therapeutic clinical trials; clinical trials of traditional Chinese medicine4. Active bacterial or fungal infection found clinically >= NCI-CTC (Common drug toxicity standards developed by the National Cancer Institute) CTCAE 5.0;5. Infection with HIV (human immunodeficiency virus), HCV (hepatitis C virus), HBV (hepatitis B virus), severe asthma, autoimmune disease, immune deficiency or patients treated with immunosuppressive drugs;6. People infected with herpes virus (except for scabs that last for more than 4 weeks);7. People with respiratory virus infection (except those who have been cured for more than 4 weeks);8. Severe coronary artery or cerebrovascular disease, or other diseases that the researcher believes should be excluded;9. Clinical, psychological or social factors affect informed consent or research conduct;10. Those with a history of drug or peptide allergy, or allergies to other potential immunotherapies;11. Patients without capacity for civil conduct.

#### Termination criteria

2.4.3

Subjects have the right to voluntarily withdraw from this clinical study:

In the event of recurrence of the original disease, adverse events, violation of the treatment plan, management or other reasons, the researcher has the right to terminate the clinical study of the subject, and at the same time detail the reasons for terminating the clinical study of the patient in the case report.

Patients will discontinue study treatment prematurely for any of the following reasons:

1. Violation of the protocol: Violation of the main content of the protocol, especially when it is related to the patient’s life safety;2. Withdraw informed consent;3. Intolerable adverse reactions, such as allergies or level 4 cytokine release syndrome;4. Lost to follow-up: unable to be contacted via regular contact methods and beyond the window period;5. Any other reasons confirmed by the researcher. Patients who withdraw early cannot be replaced by other subjects.

### Outcome measures

2.5

#### Primary study endpoints

2.5.1

Progression-free survival (PFS): (Evaluation index: RECIST 1.1, with inclusion of FDG-PET/CT).

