### Follow-up

2.6

At the end of each course of treatment, patients must return to the hospital for a visit. If necessary and the patient wishes, the trial procedure for the next course of treatment can be started. At the same time, visits must be made every 3 months after each course of treatment. Visits and examinations include blood routine, blood biochemistry, urine routine, stool routine, and coagulation function test on accompanying medications. Carcinoembryonic antigen (CEA) and other tumor markers, CD antigen, T cell activity assessment, vital signs, ECOG score, electrocardiogram, imaging examination (CT, MRI). Please refer to the visit plan for details of the visit plan (**Table 1**). When a certain assessment is required, a “ √ ” will be marked on the visit plan.

**Table 1 T1:** Visit reporting table.

Item	The end of treatment	Post-treatment visit (every 3 months)
Concomitant medication	✓	✓
Blood routine	✓	✓
Blood chemistry	✓	✓
Urine routine	✓	✓
Bowel routine	✓	
Coagulation function test	✓	
Thyroid function test	✓	
Alpha-fetoprotein	✓	
Pregnancy test	✓	
Vital signs	✓	✓
Physical examination	✓	✓
ECOG score	✓	✓
Electrocardiogram	✓	
Echocardiogram	✓	
Blood pressure detection	✓	
Film degree exam	✓	

The follow-up plan lasts for 24 months and is divided into 8 times, that is, every 3 months after the end of treatment, 10 mL of blood will be collected each time for efficacy and safety evaluation, while compliance will be assessed and combined medication status will be recorded.

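### FDG-PET/CT counts towards progression while vaccine and Poly I:C are injected at nodal basins: unless the placebo matches, reactive nodes may be read as progression more often in the vaccine arm, biasing PFS against it

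*Protocol article*

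**What the plan says.** - **Endpoint.** Primary study endpoints (2.5.1) defines PFS by "RECIST 1.1, with inclusion of FDG-PET/CT". It does not say how a PET finding counts towards progression.
- **Imaging at visits.** Follow-up (2.6) lists "imaging examination (CT, MRI" and does not mention PET. Table 1 ticks the film examination, apparently imaging, at the end of treatment but not at the three-monthly visits.
- **Injection sites.** Section 2.3.3.3 states: "The four vials of polypeptide vaccine were administered at the left axilla, left groin, right groin, and right axilla". It describes these as "lymph node-rich regions commonly used to enhance antigen presentation and immune activation".
- **Adjuvant and schedule.** Under 2.3.2 the peptides are "mixed with 500 μL of Poly I:C adjuvant at a concentration of 2 mg/mL prior to subcutaneous injection", given on days 1, 4, 8, 15 and 22 and at weeks 12 and 20. Section 2.3.3.1 says Poly I:C was chosen to activate dendritic cells and promote T-cell responses. The vaccine is "divided into 2–4 injection pools (1mL per injection"), so not every patient need be injected at all four sites.
- **Control arm.** Study design (2.2) first gives controls placebo plus conventional treatment with radiotherapy. A later paragraph of the same section describes conventional treatment plus radiotherapy and mentions no placebo. Placebo content and sites are not described.
- **Assessment.** The trial is open-label. For cross-over, progression is by RECIST 1.1 and verified by the investigator (2.2).

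**The concern.** The regimen aims to provoke an immune response, and its injection sites are nodal basins. Swollen or FDG-avid nodes there are a plausible consequence of the treatment working as intended. If PET findings can establish progression, such a node could be scored as a new lesion and so become an event on the primary endpoint. Where controls are not exposed to the same adjuvant at the same sites, the misclassification differs by arm. If only the progression date is recorded, it cannot be undone later.

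Separately, one section builds PET into the endpoint and another names the imaging without it. As written, it is unclear which patients have PET and when.

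**Working it through.** **1. Reproduce the plan's own figure.** Inputs from Sample size calculation (2.8) and Tables 2 and 3: 77 per arm; medians 4 and 8 months (HR 0.50); uniform accrual over 24 months; 36 months in total; two-sided alpha 0.025; power 0.80; loss 0.10.

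- Events needed (Schoenfeld): 4 × (2.241 + 0.842)² / (ln 0.5)² = 79.1, so 80.
- Hazards: ln 2/4 = 0.1733 and ln 2/8 = 0.0866 per month. Table 2 is matched only if the loss is 10% per month, −ln 0.9 = 0.1054.
- Probability of an observed event, with k = λ + δ: (λ/k) × [1 − (e^(−12k) − e^(−36k)) / (24k)]. Control: 0.619 × 77 = 47.6. Vaccine: 0.442 × 77 = 34.0. Total 81.6, against 47.7 + 33.9 = 81.6 in Table 2.
- Power at 81.6 events: Φ(√(81.6/4) × 0.693 − 2.241) = Φ(0.889) = 0.81. The simulated log-rank power is about 0.80; Table 3 states 0.8028.

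The base case reproduces, and the sample size calculation is not in dispute here.

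**2. Add false progression in the vaccine arm.** The documents give neither a rate nor a time, so both are assumptions. A share q of vaccine patients still progression-free is called progressed at about month 3 or about month 5. Weeks 12 and 20 are 84 and 140 days, or roughly 2.8 and 4.6 months from the first vaccination, so each time falls soon after a booster if the PFS clock starts near vaccination.

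Patients at risk of a false call (77 × share progression-free × share not lost):
- Month 3: 77 × 2^(−3/8) × 0.9³ = 77 × 0.771 × 0.729 = 43.3.
- Month 5: 77 × 2^(−5/8) × 0.9⁵ = 77 × 0.648 × 0.590 = 29.5.

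| q | False calls, month 3 | Power (HR), month 3 | False calls, month 5 | Power (HR), month 5 |
|---|---|---|---|---|
| 0 | 0 | 0.80 (0.51) | 0 | 0.80 (0.51) |
| 5% | 2.2 | 0.72 (0.55) | 1.5 | 0.75 (0.53) |
| 10% | 4.3 | 0.63 (0.58) | 2.9 | 0.69 (0.56) |
| 20% | 8.7 | 0.42 (0.66) | 5.9 | 0.57 (0.60) |

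Power is the share of simulated log-rank tests favouring the vaccine with |z| > 2.241. HR is the median observed hazard ratio, from a run with slightly different call times. That run gave power of 0.70, 0.62 and 0.40 at month 3, so the second decimal should not be leaned on.

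**3. Two variations.**
- Same q in both arms at month 3, as might follow if the placebo carried the adjuvant at the same sites: power 0.77, 0.73 and 0.66.
- No loss to follow-up, vaccine arm only, month 3: about 140 events, and power falls from 0.97 to 0.94, 0.88 and 0.71.

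**The case against.** **The arm difference is not proven.** This stands. The abstract and sections 2.2, 2.8 and 2.9 all refer to placebo. A reader might infer from the later paragraph of 2.2 that controls are not injected, and hence that the artefact is confined to the vaccine arm. The documents do not settle this, so the concern is conditional.

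**The endpoint does not say that uptake alone makes a new lesion, and a reading rule may sit in a full protocol or imaging manual.** This stands in part. The mere absence of such a rule from an article is not the point. The point is that the article fixes PET as part of the endpoint, names different imaging for follow-up, and injects an adjuvanted vaccine at nodal basins. That reactive nodes follow is an inference from the stated rationale; the documents do not report it.

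**Open-label readers may discount nodes in injected basins.** Possible, and it would lower the false-call rate. But without a common rule that discounting would itself depend on knowing the arm.

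**Month 3 is arbitrary.** Agreed: no month-3 scan is stated, and a course lasts five months. Month 5 lies closer to the ticked end-of-treatment examination and gives the milder loss.

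**Inflammatory uptake after radiotherapy.** A reader might add this to the arm bias. Both arms receive radiotherapy at both dose levels, so it does not explain a difference between them.

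**PET at each site's choice.** A reader might infer this from the mismatch between 2.5.1 and 2.6. No section says so; the mismatch supports only a request to reconcile them.

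**Conclusion.** The concern holds in conditional form. The endpoint as worded allows an intended effect of the vaccine to count as progression, and it disagrees with the follow-up section about imaging. Unless the placebo carries the same adjuvant at the same sites, the error would fall more often on the vaccine arm.

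The bias runs against the vaccine. It can hide a real effect; a reader might fear that it creates a false positive, but this mechanism does not.

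The possible size is material. Roughly two to nine false calls at month 3 would take power from 0.80 to 0.72–0.42, and roughly one to six at month 5 to 0.75–0.57. These figures rest on the assumed 5–20% range, the assumed timing, an effect in the vaccine arm only, exponential PFS, and the loss rate that reproduces Table 2. They are a sensitivity range, not a forecast.

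**What to change.** 1. Reconcile 2.5.1 and 2.6 on which imaging modalities are used for PFS.
2. For the primary PFS analysis, state that FDG-PET uptake alone does not establish progression.
3. In both arms, count new or enlarging axillary or inguinal nodes as progression only when CT/MRI size criteria are met and the finding persists or increases on the next available CT/MRI. Date progression to the first scan. Define the rule by anatomical region and not by whether a basin was injected, so that it applies identically to controls.
4. Record on the CRF the modality and lesion that established each progression, so that a sensitivity analysis including PET-only progression can be run.
5. Reconcile the two descriptions of the control arm in 2.2, and state the placebo's content and injection sites.

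**Cost.** Endpoint wording and a short CRF addition. A true nodal relapse in these regions is confirmed later, although its date is preserved. Because Table 1 does not tick imaging at the three-monthly visits, the rule refers to the next available scan; how a finding with no later CT/MRI is handled must be stated in advance. The rule is for the PFS analysis only. Its relation to the progression criterion for cross-over in 2.2 must be reconciled.
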